NCT01866982, NCT02231411, NCT02195037, [10, 11]) For example, we demonstrated a heart rate can be detected using ECG leads in the delivery room much quicker compared to an oxygen saturation monitor (pulse oximeter). [12] We have also demonstrated interventions at birth (such as squeezing or milking the umbilical cord before it is cut) that provide better blood flow in babies at 6-30 hours of life. [10] It is reasonable to infer, though it is not yet proven, that these newborns *with better blood flow* had improved brain activity and improved perfusion.

**No previous study has linked measures of brain activity and oxygenation beginning at birth to neonatal outcomes.** Newborns who require extensive resuscitation (e.g. CPR or breathing assistance) are at greater risk for hypoxic-ischemic encephalopathy (HIE) and brain injury. [13, 14] Preterm infants that require more resuscitation have a higher rate of brain bleeding and death. [15]

Heart rate by ECG (electrocardiogram) is now being recommended for use in premature newborns as a method to determine heart rate compared with conventional methods of auscultation and pulse oximetry. However it is unclear as to whether the availability of a heart rate by ECG would impact the amount of resuscitation needed by premature newborns. Therefore we will make ECG available in half of the infants (by randomization at the time of delivery by the research team, in opaque sealed envelopes) and record the amount of resuscitation needed. This will allow us to implement a recommended intervention to become our standard practice. Furthermore, since heart rate is an existing outcome in the delivery room it will not change the amount of data required for parental consent.

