| --- | --- | --- | --- |
| Gestational Age | 23 to 31+6 weeks |  | This GA most likely to require resuscitation interventions. Delayed consent will be obtained to allow for urgent unplanned deliveries to be included in the trial such as emergency C-Section, etc. |
| Parental refusal to participate |  | X | Parents may refuse participation antenatally or after delivery. |
| Congenital Anomalies |  | X | Increased risk for poor long-term outcomes and death. |
| Moderate to severe head bruising upon delivery |  | X | Difficulty in assessing skin integrity with dark bruising |

***Study Protocol:*** Currently, all infants taken to the resuscitation suite have recordings of heart rate, oxygenation, and airway pressure, along with simultaneous video recording. These recordings are reviewed monthly as part of our quality improvement process. Routine use of EEG or NIRS monitoring may be used per physician preference. Therefore the only additional component of the study will be the placement of electrodes (EEG) and a single sensor (NIRS) at the time of birth. ECG will be available in half of the infants per randomization during resuscitation. Upon identification of an eligible delivery, an additional research coordinator will be on standby to assist with placement of sensors.

EEG electrodes, NIRS probes, ECG electrodes and pulse oximetry will be applied within 60 seconds of the newborn being placed on the warmer. We piloted this procedure in four recent emergency C/S deliveries in which the research team successfully applied adhesive sensors within 60 seconds without interfering with resuscitation. The average time to display EEG and NIRS signals were 32 and 63 seconds, respectively. The placement of the sensors and tracing from one example are shown in **Figure 3**. (*Note – Removed for inclusion of protocol in publication*) While saturation and heart rate data will be available to the clinical team, data from both aEEG and NIRS will be blinded.

Additional monitoring will begin once the newborn is in the NICU. Electrical Cardiometry sensors (which can measure cardiac output and stroke volume) using four EC sensors (Electrical Cardiometry, Cardiotronic, La Jolla, CA) will be placed on the newborn’s chest.

Cerebral StO2, cardiac output, and stroke volume will be recorded every two seconds and linked with other variables that will be downloaded from the infant’s hospital bedside monitor.

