**Measured Endpoints and Recorded Outcomes**

1. Amplitude Integrated EEG signal over the first 10 minutes of life
2. Cerebral StO2 by Near-InfraRed Spectroscopy within the first 10 minutes of life
3. Resuscitation (yes/no)
4. Resuscitation score (1-6)
5. DR Interventions: PPV, CPAP, intubation, chest compressions, volume, medications (yes/no)
6. Maximum inspired oxygen (FiO2) (percentage)
7. Maximum Peak Inspiratory Pressure (cm H20)
8. Time to reach heart rate 100 beats per minute (seconds)
9. Mean Blood Pressure (by non-invasive oscillimetry) at 10 minutes
10. Cardiac Output by Electrical Cardiometry (ml/kg/min) for 72 hours
11. Cerebral StO2 by Near-Infrared Spectroscopy for 72 hours
12. EEG pattern: normal- suppressed, seizure activity for 72 hours
13. Mean Arterial Blood Pressure (mm Hg)
14. Use of cardiac inotropes (dopamine, dobutamine, epinephrine) (yes/no)
15. Presence of brain injury on MRI (yes/no) (if clinically indicated)

Our engineering collaborators will help synchronize EEG and NIRS onto the existing video-analog monitoring setup to simultaneously collect information on heart rate, body oxygenation, oxygen usage by the brain, and electrical activity of the brain. We will gather their

inpatient data to look for adverse events of premature birth and resuscitation (i.e., brain bleeding, anoxic brain injury, death) and will incorporate this data with our evaluation of the neurological and physiological data gathered during the resuscitation. Additionally, all enrolled infants will have a detailed brain ultrasound within 24 hours of birth and again at one week. An MRI will be performed when they reach full-term equivalence if clinically indicated as standard of care. The brain ultrasounds will alert us to any brain bleeding, and the MRI will reveal the full extent of any brain injury of prematurity. Given the known association between extensive resuscitation with brain bleeding and death, more evidence is needed about the physiologic responses of the brain and the body during resuscitation so that resuscitation practices can be improved to promote healthy brain development and to avoid potentially devastating outcomes.

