# Description of evaluation measures to assess project results and outcomes.

Our overall aim for this project is to provide preliminary data about the premature brain during the birth transition and resuscitation. Increased understanding of how the premature brain responds during this critical time will provide a physiological basis of improving the resuscitation process, will demonstrate the feasibility of such monitoring, and will be used to determine optimal practice for these vulnerable infants and improve their quality of life. After the successful conclusion of this project, we will apply specific interventions at birth in the preterm population and evaluate the resultant effects on neuro-monitoring. This will be in the context of a large randomized controlled trial powered to demonstrate improvements in long-term neurodevelopmental outcomes in children.

Given the known association between extensive resuscitation and outcomes such as bleeding in the brain and death, we expect to find physiological changes in newborns

immediately after birth and during the first 72 hours of life. We expect to find very early, potentially correctable changes in physiology that may be able to protect the brain before injury can take place.

We will also collect routine follow-up visit information at 18–30 months corrected gestational age to see if there is any correlation between NIRS and aEEG during the first 3 days of life to long term neurodevelopmental outcomes.

**STATISTICAL CONSIDERATIONS (Sample Size and Power Calculation):** All aspects of data

analysis and statistical investigations will be directed by [name], who has formal training in Statistics and has expertise in multivariate datasets such as these.

**Statistical Analysis**: To test the primary efficacy endpoint a 2 x 2 chi-square test will be

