conducted at each one minute interval, and the attendant effect size for the 2 x 2 contingency analyses (i.e., phi) will be reported. As well, relative risk (RR) and odds ratio (OR) statistics will be reported (along with 95 percent confidence intervals). For interval-level, continuous outcomes one-way ANOVA will be conducted and all assumptions will be tested/examined (normality, homogeneity of variance, etc.). Nonparametric options (e.g., Mann-Whitney) will be considered in case remedial measures such as transformations do not meet the parametric assumptions. We will compare continuous data measures averaged over each MOL using multi- variate linear regression analysis. We will use linear, logistic or generalized linear models to evaluate demographic variables and clinical outcome variables all using SPSS vs. 22.0 or Stata 11.0.

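### Time to heart rate 100 falls under a one-way ANOVA rule that has no value for infants who never reach 100; if they are left out, a comparison by ECG arm may be biased

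*Protocol*

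**What the plan says.** In the protocol's list of Measured Endpoints and Recorded Outcomes, item 8 of 15 is "Time to reach heart rate 100 beats per minute (seconds"). It is not named as primary. It has no observation window and no value for an infant who does not reach 100. The first ten minutes of life are named for the aEEG and cerebral StO2 signals (items 1 and 2), not for item 8.

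The Statistical Analysis paragraph chooses methods by outcome type and names no outcome:

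- Continuous outcomes: "For interval-level, continuous outcomes one-way ANOVA will be conducted".
- Fallback: "Nonparametric options (e.g., Mann-Whitney) will be considered in case remedial measures such as transformations do not meet the parametric assumptions".
- Other models: "We will use linear, logistic or generalized linear models to evaluate demographic variables and clinical outcome variables".
- Primary test: "To test the primary efficacy endpoint a 2 x 2 chi-square test will be" carried out at each one-minute interval. The endpoint itself is not named.

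No time-to-event method appears.

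On the randomised factor, the Study Protocol text says "ECG will be available in half of the infants per randomization during resuscitation". The proposal narrative gives the purpose: make ECG available and "record the amount of resuscitation needed".

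**The concern.** A time in seconds is an interval-level continuous outcome, so item 8 belongs to the ANOVA rule. ANOVA needs a number from every infant, and an infant who never reaches 100 while observed has none. The fallback does not close the gap. It responds to failed distributional assumptions, and Mann-Whitney run on recorded times omits the same infants.

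Non-reachers are foreseeable. The trial enrols from 23 weeks and expects to record chest compressions, medications and deaths. It also justifies delayed consent by the wish not to lose the sickest infants.

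Whether an infant reaches 100 is known only after randomisation and may depend on the arm. A comparison of mean times among reachers is then no longer a comparison of the randomised groups.

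**Working it through.** **Inputs.** The protocol gives 130 infants, with ECG available in half, so 65 per arm. It gives no attainment rates, times or window for item 8, and no figure for this outcome that could be reproduced. Everything else below is assumed, including a window of W = 600 s.

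**Formulas.** Let m be an arm's mean time among reachers and p its share of non-reachers; C is control, E is ECG.

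- Reachers only: D_obs = m_E − m_C.
- All infants, non-reachers set at W: D_all = (1 − p_E)m_E − (1 − p_C)m_C + (p_E − p_C)W.

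**Equal non-attainment.** If p_E = p_C = p, then D_all = (1 − p)D_obs. The sign is the same, so no reversal occurs.

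**Unequal non-attainment, worked example.** Control: 62 infants with mean 120 s and 3 who never reach 100. ECG: 62 infants with mean 110 s and 3 who reach it late, at 500 s.

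- ECG mean: (62 × 110 + 3 × 500)/65 = 8320/65 = 128.0 s.
- Control, reachers only: 120 s, so D_obs = +8.0 s (ECG looks slower).
- Control, all infants: (62 × 120 + 3 × 600)/65 = 9240/65 = 142.2 s, so D_all = 128.0 − 142.2 = −14.2 s (ECG faster).

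With a gain of g seconds in the other 62 infants, D_obs = (3 × 380 − 62g)/65. This is positive only while g < 1140/62 = 18.4 s, so a larger gain removes the reversal.

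**Simulation.** 1,000 runs per row, 65 per arm. Times are lognormal with median 110 s and log-SD 0.6. A vulnerable share, equal in both arms, never reaches 100 in control. With ECG, part of that share reaches it instead, at 360 to 600 s.

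| Never reach, control v ECG | Other times with ECG | D_obs (s) | D_all (s) | Runs with D_obs > 0 |
|---|---|---|---|---|
| 5% v 1% | unchanged | +14.2 | −4.5 | 80% |
| 5% v 1% | 5% shorter | +8.2 | −10.4 | 69% |
| 10% v 2% | unchanged | +28.2 | −11.6 | 93% |
| 10% v 2% | 10% shorter | +18.4 | −19.3 | 83% |
| 5% v 5% | unchanged | −0.6 | +0.2 | 48% |
| 10% v 10% | 20% shorter | −25.0 | −22.8 | 4% |
| none designated | 20% shorter | −24.6 | −25.4 | 3% |

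In the fourth row, ANOVA on reachers was significant in the wrong direction in 13.6% of runs. Across the rows with designated non-reachers, about 4 to 13 of the 130 infants have no time.

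**Power.** A separate simulation used lognormal times cut at 600 s, 65 per arm.

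| Analysis | Medians 150 v 100 s, log-SD 1.0 | Medians 120 v 80 s, log-SD 1.2 |
|---|---|---|
| ANOVA, raw times, reachers only | 0.42 | 0.28 |
| ANOVA, log times, reachers only | 0.51 | 0.36 to 0.37 |
| Log-rank, all infants | 0.54 | 0.42 |
| Mann-Whitney, non-reachers worst | 0.60 | 0.45 |
| ANOVA, log times, non-reachers set at 600 s | 0.62 | 0.47 |

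The protocol allows transformation, so the second row is the fair comparator. Against log-rank the gap is then 0.51 v 0.54 in the first case and about 0.36 v 0.42 in the second. The last row shows that giving every infant a value matters more than which test is used.

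**The case against.** A reader might infer that the main ECG comparison drops the sickest infants and can reverse direction. The protocol does not support that reading, for four reasons.

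1. The randomisation is tied to the amount of resuscitation needed. That corresponds to items 3 to 5 of the outcome list, which can be recorded for every infant. Time to heart rate 100 is nowhere named as the ECG endpoint, and the primary test is a chi-square at each minute.
2. Exclusion of non-reachers is not stated. A cap, a worst rank or a reached/not-reached model is not ruled out, and an SAP could specify one.
3. The ten-minute window is borrowed from other signals. Heart rate is also downloaded from the bedside monitor in the NICU. With longer follow-up there would be fewer non-reachers, perhaps mainly infants who die first.
4. Reversal needs both unequal non-attainment and late reachers. It is absent when non-attainment is equal. A large loss of power should not be claimed either, because the permitted log transformation recovers part of it.

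All four stand, and they limit the point to one recorded outcome of unknown impact. They do not remove it. The protocol does more than leave a coding detail open: it fixes, by outcome type, a method that needs a value some infants may not have, and its fallback rule does not address them.

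A further caution concerns the remedy. The narrative reports that ECG shows a heart rate sooner than oximetry. Simply giving infants already at or above 100 the time of their first reading could therefore favour the ECG arm with no physiological difference.

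**Conclusion.** The point holds in limited form. As written, time to heart rate 100 goes to one-way ANOVA, and neither that rule nor its fallback deals with infants who do not reach 100. If they are left out, a comparison by ECG arm is conditioned on a post-randomisation event and may be biased.

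The size cannot be fixed from the protocol. Under the assumed unequal rates (5% v 1% and 10% v 2%, with late reachers), the reachers-only difference ran from +8 to +28 s, against −4 to −19 s in all infants. With equal rates the two agreed closely. The case for change rests on using every randomised infant and protecting the direction of the result; power is a minor part of it. The stated ECG purpose and the primary test are not shown to be affected. This is a cheap improvement.

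**What to change.** Take time to heart rate 100 out of the ANOVA rule and add a short paragraph that covers the following:

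- **Window.** State the observation window, for example the first 10 minutes of life.
- **Analysis.** Include every randomised infant whose data may be used, in one of two ways. Either use Kaplan-Meier with a log-rank test or restricted mean time, censoring infants who do not reach 100 at the end of the window. Or use a rank test with non-reachers ranked worst.
- **Deaths.** Count death before reaching 100 as not reached, and keep that infant as a non-reacher to the end of the window.
- **Heart rate source.** Take heart rate from the same recorded source in both arms. The Study Protocol text lists ECG electrodes among the sensors applied without limiting them to one arm, so the source needs stating.
- **Already at or above 100 at first reading.** Treat these infants identically in both arms, for example as having reached 100 by that time, so that earlier ECG detection is not counted as an earlier rise in heart rate.

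No extra infants are needed, and no extra data provided a common heart rate source is recorded in both arms. The cost is a few sentences, and a result reported as a curve, a restricted mean or a rank comparison instead of a simple mean.

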# Size of the population to be studied in terms of age, gender, ethnicity, the source of subjects and the recruitment process.

In 2014 more than 9,400 babies were born at Sharp Mary Birch Hospital for Women and Newborns, and 1,500 babies were admitted into the NICU. In our most recently completed trial in premature infants with identical eligibility criteria (23-32 weeks gestation), we recruited 150 subjects in less than 2 years. (Platform Presentation: Katheria et al, E-PAS 2015). Therefore, we are confident that we will be able to enroll the 130 newborns needed over the two year grant period. This figure is also conservative to include a parental refusal rate of 20 percent since we do not anticipate many parents would refuse to participate given the minimal risks of the study. Every premature newborn from 23 to 32 weeks gestation born at Sharp Mary Birch will be considered for enrollment until we reach our target of 130 newborns over the two year period.

**Study Timeline:** We anticipate it will take 18 months to recruit 130 infants and six months to

collect and analyze data for publication and presentation at a national meeting (total 24 months). We do not anticipate that any subjects would drop out since the intervention is performed at birth.

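### The tests named for the primary efficacy endpoint and for continuous outcomes carry no covariate, so the ECG comparison, if analysed by them, gives up precision that recorded gestational age could supply

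*Protocol*

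**What the plan says.** The Proposal Narrative sets up the randomised part of the study: "we will make ECG available in half of the infants", by sealed envelope at delivery, and "record the amount of resuscitation needed". Elsewhere the protocol plans for 130 newborns.

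The Statistical Analysis paragraph, under Statistical Considerations, names these methods:

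- For the main endpoint: "To test the primary efficacy endpoint a 2 x 2 chi-square test will be" carried out at each minute, with phi, and "relative risk (RR) and odds ratio (OR) statistics will be reported" with 95% intervals.
- For other measures: "For interval-level, continuous outcomes one-way ANOVA will be conducted", with transformation or Mann-Whitney if assumptions fail.
- For continuous measures averaged over each minute of life: multivariate linear regression, with no covariates named.
- Last: "We will use linear, logistic or generalized linear models to evaluate demographic variables and clinical outcome variables". Again no terms are named.

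Gestational age is on the infant data list in Table 2. Table 1 sets eligibility at "23 to 31+6 weeks" and justifies that range by the likelihood of needing resuscitation.

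**The concern.** With two arms, one-way ANOVA is the unadjusted two-sample t-test, and the 2 x 2 chi-square is likewise unadjusted. If they are the analysis of the ECG comparison, outcome variation due to gestational age stays in the error term. The infants run from the edge of viability to almost 32 weeks, and gestational age plausibly has much to do with how much resuscitation an infant receives.

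The cost would be wider confidence intervals for the ECG effect on measures such as maximum inspired oxygen or peak pressure, and a greater chance of missing a real effect with about 65 infants per arm. The issue lies in the analysis model, not in the allocation. The precision is lost even if the arms happen to be perfectly balanced on gestational age, and stratified envelopes would not recover it unless gestational age also entered the analysis.

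**Working it through.** **Is there a figure of the plan's own to reproduce?** No. The sample size of 130 comes without an effect size, standard deviation, event rate, power or significance level, so it cannot be re-derived.

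**Inputs from the protocol.** 130 infants, half with ECG available: 130/2 = 65 per arm. No dropout is expected.

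**Assumptions, not in the protocol.** Two-sided 5% level (suggested by the 95% intervals). R², the share of the outcome's variance explained by gestational age, is varied from 0.04 to 0.4.

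**Continuous measures.** Adjustment multiplies the residual SD by √(1 − R²).

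- Standard error of the difference, in SD units, unadjusted: √(2/65) = 0.175.
- Difference detectable with 80% power, unadjusted: (1.96 + 0.84) × 0.175 = 0.49 SD.
- Interval width relative to unadjusted: √(1 − R²).
- Unadjusted sample size giving the same precision: 130/(1 − R²).
- Detectable difference after adjustment: 0.491 × √(1 − R²).
- Power at a true difference of 0.491 SD (normal approximation): Φ(2.80/√(1 − R²) − 1.96).

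| R² | √(1 − R²) | Interval narrower by | Equivalent N | Extra infants | Detectable difference (SD) | Power at 0.491 SD |
| --- | --- | --- | --- | --- | --- | --- |
| 0 | 1.000 | 0% | 130 | 0 | 0.49 | 80% |
| 0.04 | 0.980 | 2% | 135.4 | 5 | 0.48 | 82% |
| 0.1 | 0.949 | 5% | 144.4 | 14 | 0.47 | 84% |
| 0.2 | 0.894 | 11% | 162.5 | 33 | 0.44 | 88% |
| 0.3 | 0.837 | 16% | 185.7 | 56 | 0.41 | 92% |
| 0.4 | 0.775 | 23% | 216.7 | 87 | 0.38 | 95% |

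**Yes/no measures.** The primary test is binary, so a simulation compared the uncorrected chi-square with a logistic model containing arm and gestational age. It used 65 per arm and 2,000 runs per setting, with an assumed conditional log odds ratio of −0.9 for ECG and an intercept of 0.4.

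| Assumed gestational-age log odds ratio per SD | Chi-square power | Adjusted logistic power |
| --- | --- | --- |
| 0 | 69% | 70% |
| 0.5 | 65% | 70% |
| 1.0 | 56% | 64% |
| 1.5 | 41% | 56% |

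With no ECG effect, both tests rejected in 4.4% to 5.5% of runs, so the gain does not come from an inflated type I error. These figures are for the test of the conditional odds ratio. They do not measure the precision of a standardised risk difference or relative risk, which was not computed.

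**The case against.** **The paragraph never mentions ECG, arms or randomisation.** This is true. The primary efficacy endpoint is not defined there, and the primary hypothesis is predictive: low brain perfusion and activity against haemorrhage and death. The tests could be meant to compare infants with and without haemorrhage. Against that, ECG is the only randomised contrast, the word efficacy suits an intervention, and the protocol says the statistician is to be blinded to the intervention. Reading the tests as the ECG analysis is a reasonable inference, and no more.

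**Regression is already planned.** A reader might infer that every analysis ignores gestational age. The document does not support that: it plans multivariate regression for the per-minute averages, in wording that speaks of comparison, and further linear and logistic models. But it names no covariates and does not tie these models to the ECG arm, so they neither confirm nor cure the problem.

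**Covariates belong in a SAP.** In part. Naming the terms of a planned regression can be left to a SAP. The chi-square for the primary endpoint and the ANOVA for continuous outcomes, however, are fixed in the protocol, and a SAP that followed them would be unadjusted.

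**No error is shown.** A reader might infer that the unadjusted tests are biased or invalid. They are not; randomisation makes them valid. The protocol claims no power for the ECG comparison, so no stated target is missed.

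**The size is assumed.** This stands. Table 1 ties the eligibility range as a whole to resuscitation need; it does not say how strongly need varies within the range. At R² = 0.04 the power gain is under 2 points, and the 87 infants need a correlation of about 0.63 (√0.4).

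**Adjusted models can fail on rare events.** This also stands for items such as chest compressions, and the fix must allow for it.

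**Conclusion.** The point holds as a cheap improvement in efficiency. The tests that the protocol names for the primary efficacy endpoint and for continuous outcomes make no use of gestational age, which is recorded for every infant and is plausibly prognostic. That this weakens the ECG comparison rests on the inference that these tests are its analysis.

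For a continuous measure, the loss amounts to intervals about 2% to 23% wider than adjusted ones when measured against the unadjusted width, equal to about 5 to 87 infants. This assumes R² between 0.04 and 0.4 and 65 per arm. For a yes/no measure, the simulated gain in power is about 5 to 15 points at gestational-age log odds ratios of 0.5 to 1.5 per SD, again assumed, and it concerns the conditional test only. The document does not allow any of these values to be narrowed down.

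**What to change.** State in the Statistical Analysis paragraph that:

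- the ECG comparison of continuous resuscitation measures, transformed if needed, uses a linear model with ECG arm and continuous gestational age;
- yes/no measures with enough events use a logistic model with the same two terms, standardised to a risk difference and a relative risk, so that the reported effect is not only a conditional odds ratio;
- the unadjusted ANOVA and chi-square are kept as supportive analyses, and serve as the fallback where events are sparse, with a minimum event count set in advance.

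The cost is a few sentences. Gestational age is already collected and the named software (SPSS or Stata) can fit the models; no further infants or data are needed. The downside is slightly more analysis work, particularly if models are fitted minute by minute, and possibly unstable fits for rare events, which the fallback covers. Naming the covariate in advance also removes the freedom to choose covariates after seeing the data, which the present open-ended regression sentences leave.

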# The Neu-Prem Trial: Neuromonitoring of Preterm Newborn Brain During Birth Resuscitation

**Principal Investigator**: [name]

**Co-Investigators:** [name],

**Consultant:** [name]

**Length of Study**: 2 years

# Number of subjects to be studied: 130

**Age range of subjects**: Premature newborns between 23 to 32 weeks gestation

PROPOSAL NARRATIVE.

**Goals, hypothesis and objectives.** The goal for this trial is to characterize the normal brain function of 130 very premature newborns (23 to 32 weeks gestation) during the first 72 hours of life. This is the first observational study to evaluate brain perfusion and function in 130 premature newborns ***starting at the time of birth.***

Our primary hypothesis is that simultaneously recording physiological changes of the newborn (brain activity, brain oxygenation, blood pressure, blood oxygenation, cardiac function and heart rate) beginning at birth will help us predict which babies will develop adverse problems such as bleeding in the brain (intraventricular hemorrhage, IVH) and its resultant neurological problems. We hypothesize that newborns **with low brain perfusion** and **low brain activity** at birth will have **poor outcomes** such as bleeding in the brain and death. We will measure these components of brain function using two sophisticated, non-invasive technologies. First, amplitude integrated electroencephalography (aEEG), a “simplified” EEG with four sensors (single channel), enables continuous non-invasive monitoring of cerebral activity. Second, near-infrared spectroscopy (NIRS) provided by FORE-SIGHT Elite Absolute Tissue Oximeter, is another non-invasive technology that allows continuous real-time measurement of regional tissue oxygen utilization of the brain. Both technologies are FDA approved in newborns and have been predictive of brain injury or neurodevelopmental impairment. [1-9]

Our proposal builds on an ongoing research program at a nationally recognized level 3 center with the largest number of births in California. With several completed and ongoing trials in preterm infants, our group is uniquely positioned to lead this clinical trial. (ClinicalTrials.gov:

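### The regression for minute-by-minute continuous measures does not say whether an infant's minutes are pooled, tested separately or modelled jointly, and a mixed model or GEE by infant would serve better than any of the three

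*Protocol*

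**What the plan says.** The protocol fixes a method for these data in the Statistical Analysis paragraph: "We will compare continuous data measures averaged over each MOL using" multivariate linear regression. MOL is evidently minute of life.

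The measures concerned include two delivery-room items in Table 2 (Measured Endpoints and Recorded Outcomes): "Amplitude Integrated EEG signal over the first 10 minutes of life" and "Cerebral StO2 by Near-InfraRed Spectroscopy within the first 10 minutes of life". Each yields up to ten one-minute averages per infant. Table 2 also lists cerebral StO2 and cardiac output over 72 hours, and the Study Protocol text says that "Cerebral StO2, cardiac output, and stroke volume will be recorded every two seconds".

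For the binary primary endpoint the same paragraph is explicit about the time unit: a chi-square test is to be "conducted at each one minute interval, and the attendant effect size for the 2 x 2 contingency analyses (i.e., phi) will be reported". For the continuous measures there is no such statement. The paragraph names no repeated-measures method, no within-infant correlation and no significance level for this analysis. The title page gives "Number of subjects to be studied: 130".

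**The concern.** The questions asked of these series concern infants: whether the randomised ECG arms differ, or whether infants who develop IVH or die differ from those who do not. Ten values from one infant carry less information about such a difference than ten values from ten infants. If the regression counts every infant-minute as a separate observation, standard errors are too small and intervals too narrow, and a difference can be declared where none exists.

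This bears on the protocol's main hypothesis, which links low brain perfusion and low brain activity at birth to poor outcome. The sentence leaves the analyst to choose among three analyses with quite different error rates.

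**Working it through.** The protocol states no size, power or correlation for this analysis, so there is no figure of its own to reproduce.

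**Inputs.** From the protocol: 130 infants; ECG in half of them, so 65 versus 65; m = 10 one-minute averages (Table 2). Assumed: two-sided 5% level; within-infant correlation ρ from 0.1 to 0.8 if constant, or first-order autoregressive (AR(1)) with lag-one value 0.5 to 0.9.

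**Pooled reading, by formula.** For a factor that is constant within the infant, the variance of the group difference is understated by

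DE = 1 + (m − 1)ρ,

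and the actual size of a nominal 5% test is 2 × [1 − Φ(1.96/√DE)].

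- ρ = 0.1: DE = 1 + 9 × 0.1 = 1.9; 1.96/√1.9 = 1.42; size 15.5%.
- ρ = 0.5: DE = 5.5; 1.96/√5.5 = 0.84; size 40.3%.
- ρ = 0.8: DE = 8.2; 1.96/√8.2 = 0.68; size 49.4%.

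**All three readings, by simulation.** 130 infants, ten minutes, no group difference, 4,000 runs per setting. The pooled fit includes minute effects; the joint fit is a Hotelling T² test on the ten minutes.

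| Correlation | Pooled fit | Separate fits, per minute | Separate fits, at least one of 10 | Joint fit |
|---|---|---|---|---|
| Constant 0.1 | 15.9% | 4.9% | 38.8% | 4.8% |
| Constant 0.2 | 23.4% | 5.0% | 38.4% | 5.0% |
| Constant 0.5 | 40.9% | 5.0% | 29.3% | 4.7% |
| Constant 0.8 | 49.4% | 5.2% | 17.3% | 5.7% |
| AR(1) 0.5 | 21.5% | 5.0% | 35.3% | 4.8% |
| AR(1) 0.8 | 40.5% | 5.1% | 25.8% | 5.3% |
| AR(1) 0.9 | 47.7% | 5.3% | 19.8% | 5.1% |

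The Monte Carlo standard error is at most about 0.8 percentage points (√(0.5 × 0.5/4,000) = 0.008), so the ends of the ranges can move by a point or so on a repeat run. If the ten minutes were independent, the chance of at least one false positive would be 1 − 0.95^10 = 40.1%. A t-test on one mean per infant held 4% to 6% throughout.

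**Sensitivity of the pooled figure.** With five usable minutes, ρ = 0.2 gives DE = 1.8 and 14.4%, and ρ = 0.8 gives DE = 4.2 and 33.9%. Weak AR(1) correlation (0.1) with ten minutes gives only about 7%.

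**Cost of the joint reading.** Standard multivariate regression needs all ten minutes from every infant. The Study Protocol text has sensors applied within 60 seconds of placement on the warmer, and in its four-delivery pilot the EEG and NIRS signals took 32 and 63 seconds on average to appear. Early minutes, above all for StO2, are therefore likely to be missing for some infants. As illustration only: if each minute were missing independently with an assumed probability of 2%, 5% or 10%, the complete cases would be 130 × 0.98^10 = 106, 130 × 0.95^10 = 78 or 130 × 0.90^10 = 45. Gaps clustered in the same infants would cost fewer.

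**The case against.** The strongest reply is that the protocol says neither ordinary nor pooled. Its term, read literally, is a joint model for the ten minutes, which allows for within-infant correlation. The neighbouring chi-square tests are run minute by minute, which suggests one regression per minute with one row per infant. Both readings keep about 5% per test. This stands. A reader might infer that the plan itself treats the minutes as independent and so carries a 20% to 50% false-positive rate. The document does not support that: the inflation belongs to one of three readings and depends on a correlation that the protocol does not give.

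Two further extensions also fail:

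- The statement "We will use linear, logistic or generalized linear models to evaluate demographic variables and clinical outcome variables" concerns variables that are largely recorded once per infant, for which independent rows are correct. It is not part of this point.
- The two-second recording rate describes data capture. Nothing says that raw readings enter a model, so no error rate follows from the number of readings.

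It can also be said that a correlation structure is commonly left to the statistical analysis plan, which is not shown and may settle the matter. That limits the weight of the point but does not remove it, because the protocol does not leave this method open. It names one, in a sentence that admits analyses with very different properties.

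**Conclusion.** The concern holds as one of ambiguous wording with a better method at hand. It does not hold as a demonstrated invalid analysis.

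- If pooled in an ordinary fit, an infant-level comparison would reject a true null about 16% to 50% of the time, assuming ten minutes, a constant correlation of 0.1 to 0.8 and a two-sided 5% level. Fewer usable minutes or weak serial correlation give less. A group-by-minute interaction or a within-infant time effect would behave differently.
- If fitted minute by minute, each test is valid, but there is no overall test and no rule for the roughly 17% to 39% chance of at least one false positive.
- If fitted jointly, size is nominal, at the price of every infant with a gap.

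Whether the sentence also covers the 72-hour series is not stated. If it does, 72 × 60 = 4,320 minutes per infant cannot be modelled as joint outcomes on 130 infants, and 4,320 separate tests would give about 0.05 × 4,320 = 216 false positives in expectation if no minute differed.

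**What to change.** Replace the sentence with, for example: *Minute averages of cerebral StO2, aEEG amplitude and other continuous measures will be analysed with a linear mixed model (or GEE) with infant as the correlated unit and fixed effects for minute, group and group-by-minute. One overall group test will be reported. The 72-hour series will be reduced to prespecified epoch averages and analysed in the same way.* The text should also define the overall test, for instance as the group difference averaged over the ten minutes, and name the covariance structure.

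The mixed model uses infants with some minutes missing, provided that missingness can be taken as explained by the observed data. Both packages that the protocol names can fit it. Adjustment for gestational age is optional and not part of this correction.

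The cost is one sentence, slightly more analysis work, and wider intervals than a pooled fit would give: by a factor of about √1.9 = 1.4 to √8.2 = 2.9 over the assumed constant correlations. That width reflects the information actually available on the comparison.
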